### Reference standard

The reference standard is determined by an expert panel comprising five senior consultants (with a minimum of 5 years of clinical experience). A consensus of diagnosis and triage is required from at least three out of these five experts after a comprehensive review of the patients' medical histories. In cases where expert consensus cannot be achieved, patients will be asked to attend follow-up appointments, during which additional examinations may be recommended. If, after 3 months of follow-up, a definitive diagnosis remains elusive, the patient will be excluded from the study.

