## Methods and analysis

### Objectives

Our study consists of a development stage and two evaluation stages of cross-sectional study (Figure 1):

(1) During the *in silico* development stage, we aim to develop a multimodal AI system using ChatGPT and anterior segment images captured in medical facility to facilitate the diagnosis and triage of ophthalmic diseases.(2) During the first evaluation stage (silent evaluation), we aim to evaluate the AI system's performance based on medical histories obtained through observation without patient interaction and anterior segment images captured in medical facility.(3) During the second evaluation stage (early clinical evaluation), we aim to evaluate the AI system's performance in outpatient clinics based on medical histories obtained through patient interview and smartphone-captured anterior segment images.

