### Eligibility criteria

Medical dialogues in the development stage should comply with the following criteria: (1) Inclusion criteria: We will include dialogues from both initial consultations and follow-up visits that provide adequate medical history information while minimizing the inclusion of physical examination details. The diagnosis should correspond to diseases ranked within the top 5 outpatient cases for each subspecialty, based on data from the Eye & ENT Hospital of Fudan University over the past 3 years. (2) Exclusion criteria: we will exclude diseases that are diagnosed or triaged solely based on physical examinations.

Anterior segment images in the development stage should comply with the following criteria: (1) Inclusion criteria: Individuals should have a documented medical history and diagnosis; Following a review of the medical history, both the diagnosis and subspecialty triage should have been confirmed according to the reference standard, as specified below. (2) Exclusion criteria for anterior segment images: photos with insufficient lighting or facial covering.

In the silent evaluation and early clinical evaluation stages, all cases should adhere to the following criteria: (1) Inclusion criteria: informed consent must be obtained from all participants; participants should have specific concerns or issues directly related to their eyes; for patients who are unable to provide informed consent due to incapacity or are underage or otherwise vulnerable, consent from must be obtained from their legal guardians and legal guardians are required to assist in the collection of medical history and images; each participant's diagnosis and subspecialty triage must be validated using a reference standard as detailed below. (2) Exclusion criteria: cases where the diagnosis and triage results fail to generate due to a program error; patients who, in the opinion of the attending physician or clinical study staff, are too medically unstable to participate in the study safely; diseases with prevalence below the 5-percentile threshold are not included.

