### Data management

The research consortium organizes a central data management board, and the contact details of its members can be obtained from the consortium coordinator, [name]. Electronic medical records data for all recruited subjects will be securely stored in password-protected files on the hospital's local server. Access to these files will be restricted to researchers with the explicit consent of the subjects. Survey data, both input and output from the multimodal AI system, will be stored in a secure public server (aliyun.com). To safeguard patient privacy, we will not collect any Protected Health Information (PHI), including the patient's name, date of birth, and medical insurance number. The anterior segment images captured by either slit-lamp or smartphones will undergo digital masking to irreversibly remove identifiable features, while preserving disease-relevant features essential for diagnosis. To further ensure data security, clinical researchers, trained in data management, will utilize password-protected smartphones for data entry. The smartphone is securely stored in a cabinet with password protection and is not permitted to be taken outside of the research site. Data integrity will be rigorously maintained through a variety of mechanisms, including referential data rules, valid values, range checks, and consistency checks against data already stored in the database.

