### Adverse event monitoring

The multimodal AI system doesn't disrupt standard patient management procedures, ensuring the integrity of diagnosis and treatment. Patients in the study also benefit from thorough medical history reviews by five expert clinicians, enhancing the standardization of their care. The major adverse events may stem from biased outputs and misinformation produced by language models. All participants (including researchers) in this study are encouraged to report any toxic information generated by the multimodal AI system, such as unhelpful information that fails to assist users in their tasks, dishonest information that fabricates or misleads users, and harmful information that can lead to physical, psychological, or social harm to individuals or the environment. In our prompt engineering process, we will include a fine-tuning phase to iteratively enhance content quality. Collecting toxic content is helpful for identifying areas for improvement and making necessary adjustments. Therefore, the fine-tuning process based on toxic content may facilitate adapting our AI system to real-world use and mitigating potential harms.

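### The reference diagnosis is described as a review of medical histories, while the Blinding section implies a wider record; the panel's evidence should be stated and should include examination findings for every patient

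*Protocol article*

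**What the plan says.** The Reference standard section of the protocol article sets the reference by a panel of five senior consultants. At least three must agree on diagnosis and triage "after a comprehensive review of the patients' medical histories". The section names no examination finding or image that the panel must see.

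If agreement is not reached, "patients will be asked to attend follow-up appointments, during which additional examinations may be recommended". The section ends: "If, after 3 months of follow-up, a definitive diagnosis remains elusive, the patient will be excluded from the study".

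The Eligibility criteria require every participant in both evaluation stages to be validated against this standard. The Blinding section describes the panel's information differently: the assessors know the patient's clinical information and are kept unaware of the AI output. That term is not defined, and the same section uses it for what the researchers entering data into the AI may see.

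The AI's own inputs are history and images. In the silent evaluation it is assessed "based on medical histories obtained through observation without patient interaction and anterior segment images captured in medical facility". In the early clinical evaluation the history comes from patient interview and the images from a smartphone.

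**The concern.** Every accuracy figure in the study, including the primary outcome, is measured against this reference. If the panel works from history alone, two things follow.

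- **Correlated error.** The panel and the AI's text component draw on the same type of information. A patient who under-reports or exaggerates symptoms, which the Limitation section itself expects, can mislead both in the same direction. Shared errors of this kind count as correct AI results.
- **Unchecked consensus.** Three experts who agree on a wrong diagnosis end the process. Only cases without agreement may receive further examination, so nothing requires a confident error to be tested against examination findings.

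Panel errors that the AI does not share work the other way: a correct AI answer is scored as wrong. The reported sensitivity could therefore lie on the wrong side of its target in either direction.

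**Working it through.** The plan states no panel accuracy, so there is no figure of its own to reproduce. The check is first textual, then illustrative.

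**1. What medical history means in this protocol**

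- Objectives: the AI inputs are listed as history and, separately, anterior segment images.
- Eligibility criteria: development dialogues should give enough history while keeping physical examination detail to a minimum, so the two are distinct.
- Recruitment: in the early clinical evaluation, researchers gather history and also take images. The outpatient physician's diagnosis comes afterwards and is not said to feed the reference.
- Blinding: the panel knows the clinical information, a broader and undefined term.

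The first three favour a narrow reading of the Reference standard section and the fourth a wide one. The text does not settle which applies.

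**2. Overall agreement with an imperfect panel**

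Assumed inputs: true AI correctness 0.70; panel error rate e = 0.10, 0.15 or 0.20; c = chance that the AI repeats the panel's error; P = chance that the AI is right when the panel is wrong. Only the 75% target comes from the plan (Hypotheses, early clinical evaluation).

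When the panel is right, the AI agrees with probability a = (0.70 − eP)/(1 − e). The apparent value is (1 − e)a + ec = 0.70 + e(c − P).

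| c | P | e = 0.10 | e = 0.15 | e = 0.20 |
|---|---|---|---|---|
| 0.7 | 0.2 | 0.750 | 0.775 | 0.800 |
| 0.5 | 0.3 | 0.720 | 0.730 | 0.740 |
| 0.1 | 0.7 | 0.640 | 0.610 | 0.580 |

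The bias is zero when c = P. Lifting 0.70 to 0.75 needs e(c − P) ≥ 0.05, that is c − P ≥ 0.50 at e = 0.10 and ≥ 0.25 at e = 0.20. Only the first row gets there. This model describes overall agreement, not the one-vs.-rest sensitivity to which the target applies.

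**3. One-vs.-rest sensitivity**

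Take the AI's true sensitivity S = 0.75 and specificity C = 0.95 (the targets in Hypotheses). Assume prevalence π = 0.10 and panel sensitivity Sr and specificity Cr. With J1 and J0 the probabilities that AI and panel are both positive in diseased and non-diseased patients:

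apparent sensitivity = [πJ1 + (1 − π)J0] / [πSr + (1 − π)(1 − Cr)]

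Independent errors give J1 = S·Sr and J0 = (1 − C)(1 − Cr). Fully shared errors give J1 = min(S, Sr) and J0 = min(1 − C, 1 − Cr).

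For Sr = 0.95 and Cr = 0.99 the denominator is 0.095 + 0.009 = 0.104. Independent: (0.07125 + 0.00045)/0.104 = 0.69. Fully shared: (0.075 + 0.009)/0.104 = 0.81.

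| Sr / Cr | independent | halfway | fully shared |
|---|---|---|---|
| 0.95 / 0.99 | 0.69 | 0.75 | 0.81 |
| 0.90 / 0.98 | 0.63 | 0.75 | 0.86 |
| 0.80 / 0.97 | 0.57 | 0.76 | 0.95 |

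Over prevalence 0.05 to 0.25 the independent case gives 0.46 to 0.73 and the fully shared case 0.80 to 0.96, against a true 0.75. Both models agree that the sign depends on how far errors are shared, which the documents do not tell us. Full sharing is a bound, not an expectation.

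**The case against.** The strongest reply is that the text does not forbid the panel from seeing examination findings. Blinding gives it clinical information. Further examinations described as additional may mean beyond those already done. These are outpatients in ordinary care, and "Electronic medical records data for all recruited subjects will be securely stored". A condensed article may leave the panel's dossier to the full protocol. This stands in part: history-only review is the literal reading, not an explicit ban. But the section that defines the reference does name its basis, and that basis differs from the Blinding wording.

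Four stronger readings are tempting and are not supported.

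- *The panel reads the same history as the AI.* No section says so. In the silent stage, researchers answer the AI's queries from the observed dialogue. In the early clinical stage, they collect answers before the physician's consultation. The AI also uses images. Only the type of information is shared.
- *Other sections confirm the narrow basis.* The Eligibility sentence "Following a review of the medical history, both the diagnosis and subspecialty triage should have been confirmed according to the reference standard" concerns development-stage images and itself defers to the reference standard. The phrase "thorough medical history reviews by five expert clinicians" under Adverse event monitoring is a passing remark on patient benefit. The Reference standard section carries the point alone.
- *The AI result influences how patients are verified.* The panel is blinded to AI output, so the route depends on its own disagreement. Stepped adjudication is a common design, and the fix keeps it.
- *The anterior-versus-posterior subgroup comparison suffers most.* The documents give no reference quality by lesion location, so this cannot be shown.

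**Conclusion.** The point holds as an inconsistency to reconcile and a weakness in the reference if the defining section is followed literally. In that case the reference and the AI's text input share a type of information, errors may be correlated, and a wrong consensus need not meet any examination finding.

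A reader might infer that sensitivity will be inflated past its target. The documents do not support that. The illustrative spread of 0.58 to 0.80 straddles the assumed truth of 0.70, and the one-vs.-rest model returns about 0.75 when errors are shared halfway at 10% prevalence. Size and direction rest on e, c and P, none of which the plan gives. The case for change is that the uncertainty touches the primary outcome and is cheap to reduce. It should be corrected; confidence is moderate, because the full protocol may already provide for it.

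**What to change.** In the Reference standard section, state that for every patient in the silent and early clinical evaluations the panel sets diagnosis and triage from the complete outpatient record: the history, the treating physician's examination findings and any tests already done, with the AI output removed. This should apply whether or not the experts would have agreed on history alone. Use the same description in the Blinding section, so that the term for what the panel knows has one meaning and is distinguished from what the data-entry researchers see. Leave the existing follow-up step for unresolved cases as it is.

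The cost is a change of wording and somewhat more reading time for five experts. No new examination is called for, because routine care produces these findings (Recruitment) and electronic records are kept for all recruited subjects (Data management). That section limits file access to researchers with the subjects' explicit consent, so panel access should be confirmed as covered. If the full record was always intended, the change is a single clarifying sentence.

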### Index test

During the *in silico* development stage, the index test refers to either the ChatGPT-based medical inquiry system or the image-based system utilizing anterior segment images acquired via slit-lamp or camera in medical facility for ophthalmic disease diagnosis and triage. During the silent evaluation stage, the index test refers to a multimodal AI system that integrates the aforementioned components for diagnosis and triage. During the early clinical evaluation stage, the index test refers to an upgraded multimodal AI system capable of analyzing anterior segment images obtained through smartphones.

### Outcome measure

The primary outcome is the correctness of the AI system's diagnosis, and the secondary outcome is the correctness of the AI system's triage decisions. The above assessment takes place by comparing the AI-generated results with the reference standards established by expert panels:

(1) Judged as correct: when the system's results are entirely consistent with the reference standard; when the system's results fall within the range of the reference standard.(2) Judged as incorrect: when there is no overlap between the system's results and the reference standard; when the system fails to provide any diagnostic or triage information.(3) In the following scenarios, additional discussion and assessment are required. A consensus is considered to be reached when at least 2 out of 3 experts are in agreement: when the reference standard includes the system's results; when there is partial overlap between the system's results and the reference standard.

In addition to assessing accuracy, we will also evaluate the quality, empathy, and patient satisfaction of the AI system's responses. Three independent evaluators (licensed healthcare professionals), who are blinded to the accuracy of the responses, will judge both “the quality of information provided” (very poor, poor, acceptable, good, or very good) and “the empathy of information provided” (not empathetic, slightly empathetic, moderately empathetic, empathetic, and very empathetic) on a scale of 1–5. Notably, these quality and empathy rating assessors evaluate the quality and empathy of the AI results based solely on the AI output, without knowledge of the patient's complete clinical information, reference standard results, or the correctness of the AI output.

During the early clinical evaluation stage, patient satisfaction (not satisfied, slightly satisfied, moderately satisfied, satisfied, and very satisfied) will be measured on a scale of 1–5 after AI responses have been generated. When evaluating satisfaction of the AI output, the patients are only aware of the AI output and remain uninformed about the reference standard results or the correctness of the AI output. After the evaluation, they can be informed of the reference standard results and the correctness of the AI output.

### Blinding

The blinding methods vary depending on the roles of the researchers and the stage of the study in which the researchers and subjects are involved. AI developers and AI output correctness assessors have access to complete patient information, including medical history, reference standard results, and AI output for determining correctness.

In our study, two roles are subject to blinding. (1) Reference standard assessors: These assessors possess knowledge of the patient's clinical information but are unaware of the AI output or its correctness. This approach helps mitigate information bias and classification bias. (2) Clinical researchers: These researchers are responsible for inputting data into the multimodal AI program. During the *in silico* development stage, they have access to all patient clinical information and reference standard results. However, during the silent evaluation and early clinical evaluation stages, they only have access to the patient's clinical information without knowledge of the reference standard. This approach helps mitigate diagnostic suspicion bias.

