#### Early clinical evaluation

The mobile mini-program will be upgraded to analyze anterior segment images obtained by smartphone-based devices. An early clinical evaluation of this upgraded program will be simultaneously conducted as a cross-sectional study at three sites: the Eye & ENT Hospital of Fudan University (Shanghai), the Affiliated Eye Hospital of Nanjing Medical University (Nanjing), and Suqian First People's Hospital (Suqian). During the study, researchers will interact with patients to collect necessary information for completing the queries generated by the AI system. Anterior segment images will be captured for each patient by researchers using smartphones (Figure 4). The images should be captured by the macro lens of the smartphone. The positions of both eyes should align with the eye locations specified on the smartphone screen. The images should be large enough to provide a clear view of the affected area of the diseased eye. For all stages, the reference standards of disease diagnoses and subspecialty triage will be determined by an expert panel comprising ophthalmic specialists with a minimum of 5 years of clinical experience. Upon the completion of these data collections, a separate expert panel will assess the accuracy of AI intelligent diagnosis and triage.

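### The experts who settle discretionary cases for the primary outcome are unmasked: they have the AI output, the reference result and the full patient record

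*Protocol article*

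**What the plan says.** All references are to the protocol article.

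- **Outcome measure** defines the endpoint: "The primary outcome is the correctness of the AI system's diagnosis, and the secondary outcome is the correctness of the AI system's triage decisions". Rule (1) scores as correct an answer identical to the reference or within its range. Rule (2) scores as incorrect an answer with no overlap, or no answer at all. Rule (3) sends two remaining situations to discussion: "when the reference standard includes the system's results; when there is partial overlap between the system's results and the reference standard". There, "A consensus is considered to be reached when at least 2 out of 3 experts are in agreement".
- **Blinding** sets out what the scorers see: "AI developers and AI output correctness assessors have access to complete patient information, including medical history, reference standard results, and AI output for determining correctness". It continues, "In our study, two roles are subject to blinding", and names the reference standard assessors and the clinical researchers who enter data. Of the reference standard assessors it says: "These assessors possess knowledge of the patient's clinical information but are unaware of the AI output or its correctness".
- **Early clinical evaluation** adds that "a separate expert panel will assess the accuracy of AI intelligent diagnosis and triage", so the scorers are not the people who set the reference.

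**The concern.** Rule (3) cases are decided by judgement. An expert who knows which answer is the AI's may be lenient towards it or hard on it, and open discussion before a vote lets one view carry the others.

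The full record adds a second route. The task is to compare the AI answer with a reference that has already been settled. With the chart in hand, an adjudicator can instead ask whether the AI's answer is defensible for this patient. That reopens the reference after the AI's answer is known, which is what masking the reference panel is meant to prevent.

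At stake is the credibility of the sensitivity and specificity set against the targets in Hypotheses, to the extent that rule (3) cases contribute to them.

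**Working it through.** The plan gives no figure to reproduce on this point. The check is a reading of the sections side by side, followed by one piece of arithmetic on how far rule (3) cases could move a result.

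**1. Are the scorers masked?** Blinding lists the reference result and the AI output as separate items available to the correctness assessors, together with complete patient information. It names two blinded roles, and this is neither of them. I take the three experts of rule (3) to be these correctness assessors. That is the natural reading, though the article does not say so in one sentence.

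**2. Which decisions are exposed?**

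| Situation (Outcome measure) | How scored | Exposed? |
|---|---|---|
| Identical to reference | Fixed: correct | No |
| No overlap, or no output | Fixed: incorrect | No |
| Reference includes the AI result | Discussion, 2 of 3 | Yes |
| Partial overlap | Discussion, 2 of 3 | Yes |

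Rule (1) also accepts an answer within the range of the reference. That appears to describe the same relation as the third row of the table, so the entry point to rule (3) is not sharply drawn. The point made here concerns cases that do enter rule (3).

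**3. Does scoring need the source labels and the record?** It needs both answers. It also needs direction, because an AI answer narrower than the reference is not treated like one that is broader. Direction can be restored after the vote: experts record how A relates to B, and the key then shows which was the AI's. The article gives no reason why the full record is needed for this comparison.

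**4. How far could rule (3) cases move a result?** For one disease, let n be the reference-positive cases, c those scored correct by fixed rule, and a those sent to rule (3). Then:

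- all adjudicated cases incorrect: sensitivity = c/n
- all adjudicated cases correct: sensitivity = (c + a)/n
- width of the interval = a/n

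Sample size calculation gives 22 per disease for the silent evaluation, so each adjudicated case adds 1/22 = 4.5 percentage points of width. The 85% target corresponds to 0.85 × 22 = 18.7, that is 19 correct. Here 19/22 = 86.4% and 18/22 = 81.8%, so a single decision can separate meeting the target from missing it.

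This is a bound on what adjudication can decide and not an estimate of bias. The article does not give a, nor any information on how masked and unmasked experts would differ.

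**The case against.** Several arguments on the other side stand.

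- **Safeguards exist.** The reference panel does not see the AI output, the scoring panel is separate, clear cases follow fixed rules, a majority is required, and there is no comparator arm to favour. These confine the exposure to rule (3). They do not remove it, since neither separation nor a vote after open discussion hides which answer is the AI's.
- **Correctness has a direction.** Asking only whether two unlabelled answers are equivalent would change the primary outcome. This is right, and the fix has to preserve direction and cover both rule (3) situations.
- **Labelled presentation is not literally stated.** The article says what assessors have access to, not how it is laid out. Even so, it lists the two items separately and omits this role from the blinded ones. That is a stated design choice, not a detail left to a fuller document.
- **Chart context may help** in judging whether a partial match captures the presenting problem. This is a real, small cost of masking.
- **Adjudicated counts and bounds usually sit in an analysis plan.** Their absence here is no finding. They appear below only as part of the remedy.

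Two stronger readings fail. A reader might infer that rule (3) is the only subjective step. It is not: the reference itself is a 3-of-5 expert consensus, and the within-range call in rule (1) also needs judgement. A reader might also infer that the quality and empathy raters receive a masking that the primary outcome is denied. Those raters are masked to clinical information, reference and correctness, but they know they are rating AI output, so they are not masked to source either.

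**Conclusion.** The concern holds for rule (3) cases. For these, the plan openly leaves the experts who decide the primary outcome unmasked to source and gives them the full record. Bias could run either way.

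Its size cannot be stated. The share of adjudicated cases and the effect of unmasking are both absent from the article, and any percentage-point figure would rest on assumed inputs. A reader might infer that the primary outcome as a whole is compromised, or that the results will flatter the AI. The documents support neither reading, because clear matches and clear misses are fixed by rule and the reference is set blind to the AI.

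The conclusion assumes that the three experts are the correctness assessors of the Blinding section and that they see the two answers identified by source. Both are the natural reading of the text. The change is worth making because the step serves the primary outcome and the remedy is cheap.

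**What to change.** For both rule (3) situations:

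1. Reduce the AI answer and the reference to coded diagnosis or triage labels. Show them as A and B in random order, without source and without the full record.
2. Have each of the three experts record independently, before any discussion, how A relates to B: equivalent, A narrower, A broader, partial overlap that shares the main diagnosis, or partial overlap that does not.
3. After unmasking, convert the recorded relation to correct or incorrect by a rule written in advance. This keeps the direction that Outcome measure requires. The same rule should settle where within-range answers under rule (1) end and rule (3) begins.
4. Amend Blinding to list correctness assessors as masked to source at this step.
5. Report the number of adjudicated cases, and recalculate sensitivity and specificity with all of them scored incorrect and then with all scored correct.

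The cost is one administrative step and some wording in Outcome measure and Blinding. The same three experts can do the work from AI outputs that Data management already says are stored, with no new patient contact. The downside is that adjudicators lose chart context for these cases.
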